***3.3 Recruitment and randomisation***

Participants will be recruited via the online recruitment system of the Department of Psychology (BAPS-Sona, http://baps.sona-systems.com) and in lectures at the University of Basel. Subjects interested in participating in the study can sign up by e-mail. All interested subjects will be screened for inclusion and exclusion criteria and be informed verbally about the goal and the procedure of the study by telephone interview. In case of willingness to participate in the study, subjects receive a written description of the study aims, theoretical background as well as employed psychotherapeutic methods and experimental procedures (i.e. randomization and TSST) as well as the written informed consent and the a link to the baseline assessments (see below).

Upon receipt of the signed written informed consent and the filled-out questionnaires, participants will be randomized through individual assignment codes in properly concealed between black sheets, stored in sequentially numbered envelopes. After randomization, participants will be informed about study dates, thus dates for the tend-and-befriend training (TBT) and the TSST. The study participation is voluntary. Subjects can end their participation anytime and without any reason and disadvantage. The participation can be ended by the study staff when participation might have detrimental effects (e.g. participants appears to be in psychosocial crisis), the study design is not followed and in case of adverse events. The participation in the study must be ended if in retrospect the inclusion criteria do not apply to the subject or if one exclusion criterion is met.

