***3.1 Study design and data analysis***

This study is an experimental study with parallel groups. Subjects are randomized into the two conditions: Treatment condition, thus receiving tend-and-befriend training (TBT) *before* the TSST; control conditions = waitlist controls receiving tend-and-befriend training (TBT) after the termination of the study. Two weeks after the participants of the treatment condition have received the tend-and-befriend training (TBT), all participants of the treatment as well as the control condition will undergo a standardized psychosocial stress test, the Trier Social Stress Test (TSST, Kirschbaum et al., 1993). The study variables are displayed in Table 1, the flow through the study is shown in Table 2.

Table 1. Study variables

| Variables | Description | Time |
| --- | --- | --- |
| Independent Variable | Tend-and-befriend training (TBT) and waitlist control condition (WL-CC) | TBT two weeks before TSST, WL-CC after termination of study |
| Primary outcome | Cortisol and alpha-amylase | 9 measurements before, during and after TSST |
| Secondary outcomes | Psychophysiological parameters (heart rate, electrodermal activity, electrocardiography, electromyography, respiratory activity and skin temperature) | Repeated assessment before, during and after TSST |
|  | Questionnaires (PASA, STAI X-1, STAI X-2, PSS, FSozU, BFW/E, ASS-SYM) | TSST: PASA, STAI X-1  Baseline, post and follow-up: STAI X-2, PSS, FSozU, BFW/E, ASS-SYM |

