***3.2 Data analysis and sample size estimation***

Multivariate analyses of covariance and variance for repeated measures will be computed to analyse endocrine and psychophysiological stress responses as well as pre-post changes of psychometric scores between groups, controlling for differences in baseline levels when indicated. Regression analysis will be used to assess associations between psychological and cortisol parameters. For cortisol and psychophysiological parameters, areas under the response curve will be calculated with respect to increase (AUCi) and ground (AUCg), using the trapezoidal method as an indicator for the integrated biological and physiological response in the TSST (Pruessner, Kirschbaum, Meinlschmid, & Hellhammer, 2003). Data will be tested for normal distribution and homogeneity of variance using the Kolmogorov-Smirnov test and Levene’s test before statistical procedures were applied. Based on previous own studies (Gaab et al., 2003, Hammerfald et al., 2006, Storch et al., 2007), we expect a large multivariate effect size (f^2^=0.35), Therefore, the optimal total sample size of N = 48 to detect an expected large effect size of f2 = 0.35 (representing a large effect size) with a power = 0.85 and α = 0.05 was calculated a priori with the statistical software G-Power (Buchner et al., 1997). For all analyses, significance level is α = 5%. All analyses are performed according to the principle of intention to treat, with last observations carried forward when follow-up data were missing.

*Table 2: Flow through the study*

|  | TBT | WL-CC | |
| --- | --- | --- | --- |
| Baseline assessment | Advertisement with bulletins and BAPS  Information about study procedure on BAPS, screening for inclusion- and exclusion criteria on BAPS  STAI X-2, PSS, FSozU, BFW/E, ASS-SYM | | |
| Intervention | TBT | | - |
| Stress test | TSST  Assessment of 9 saliva samples -30, -20, -10, 0, 10, 20, 30, 45 and 60 min (with 0 min being directly post-TSST) for salivary free cortisol and alpha-amylase.  Continuous assessment of psychophysiological parameters (heart rate, electrodermal activity, electrocardiography, electromyography, respiratory activity and skin temperature)  Questionnaires: PASA (once), STAI X-1 | | |
| Post assessment | STAI X-2, PSS, FSozU, BFW/E, ASS-SYM | | |
| Follow-up assessment | STAI X-2, PSS, FSozU, BFW/E, ASS-SYM | | |

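### Ending a randomised woman's participation before the stress test leaves her without a primary outcome, which defeats the promised intention-to-treat analysis in practice

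*Protocol*

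**What the plan says.** Section 3.2 of the protocol fixes the analysis principle: "All analyses are performed according to the principle of intention to treat, with last observations carried forward when follow-up data were missing".

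Section 3.3 places randomisation after screening, consent and the baseline questionnaires: "Upon receipt of the signed written informed consent and the filled-out questionnaires, participants will be randomized". It then gives two rules under which a woman can be stopped after allocation.

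- A discretionary rule: "The participation can be ended by the study staff when participation might have detrimental effects". The same sentence extends this to cases where "the study design is not followed and in case of adverse events".
- A mandatory rule: "The participation in the study must be ended if in retrospect the inclusion criteria do not apply to the subject". The same obligation holds for a woman to whom any exclusion criterion applies.

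Table 1 in section 3.1 names cortisol and alpha-amylase as the primary outcome, with "9 measurements before, during and after TSST". Table 2 shows only questionnaires at baseline. The training arm is trained before the TSST and the waitlist arm after the study has ended.

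The protocol does not say that a woman whose participation is ended leaves any analysis. Nor does it say whether she is still asked to attend the TSST.

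**The concern.** Non-adherence is one of the events that an intention-to-treat analysis exists to absorb. A rule that lets staff stop a woman because she has not followed the design works against that principle if stopping her also stops her outcome from being measured. In this trial it does, because the primary outcome is collected on one occasion, at the end.

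The loss could also be unequal. Before the TSST only the training arm has sessions to miss. If staff used their discretion on poor attenders, the analysed training arm would lean towards adherent women, while the waitlist arm would stay closer to what was randomised. Randomisation would then no longer protect the comparison, and at about 24 women per arm a few removals are enough to matter.

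**Working it through.** **1. Can the stated missing-data rule fill the gap?** Carrying a last observation forward needs an earlier observation of the same variable. For the trait and well-being questionnaires there is a baseline value. For cortisol and alpha-amylase the first sample is taken 30 minutes before the TSST, on the test day itself (section 3.2, Table 2). A woman stopped before that day has no value to carry. She can be counted in an intention-to-treat set but cannot contribute an observed primary outcome.

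**2. Which arm is exposed to each trigger?**
- Design not followed: the attached manual lists six sessions of 4 + 2 + 2 + 2 + 2 + 4 = 16 hours, all before the TSST and all in the training arm. The waitlist arm has nothing comparable to miss.
- Adverse events: section 4 describes an e-mail enquiry after the training and an interview after the TSST. Before the TSST only the training arm has had any training.
- Retrospective ineligibility: the rule applies to both arms, and both are seen at the TSST. Only the extra contact during training could make detection unequal.

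**3. Scale.** The plan's N = 48 (f² = 0.35, power 0.85, α = 0.05) cannot be reproduced uniquely, because the numerator degrees of freedom u are not given. With a noncentral F and λ = f² × N, the required N is 28 for u = 1, 47 for u = 5 (power 0.860 at 48) and 51 for u = 6. The point does not rest on this figure. It uses f² only as a yardstick: for two equal groups, d = 2 × √0.35 = 1.18.

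**4. Illustration.** Assumed, because the protocol gives no removal rate and no allocation ratio: 24 women per arm; 4 of the training arm stopped before the TSST (4/24 = 17%); those 4 would have responded 0.5 to 1.0 SD more than the rest.
- Shift in arm mean = removed fraction × difference.
- (4/24) × 0.5 = 0.083 SD; (4/24) × 1.0 = 0.167 SD.
- Relative to d = 1.18: 0.083/1.18 = 7%; 0.167/1.18 = 14%.

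**5. A second way to the same range.** Suppose instead that only the training arm loses women, that there is no true effect, and that the tendency to be removed correlates r = 0.3 to 0.5 with stress reactivity (all assumed). For a removed share q, the shift is −r × φ(z₁₋q)/(1 − q).

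| Share removed | Shift in arm mean (SD) | Simulated two-sided type I error |
| --- | --- | --- |
| 10% (2 of 24) | −0.06 to −0.10 | 0.053 to 0.061 |
| 20% (5 of 24) | −0.11 to −0.18 | 0.067 to 0.088 |

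**6. Power.** Losing 4 of 48 women takes power from 0.860 to 0.818 under the u = 5 reading. In a two-group t test at d = 1.18, losing 4 from one arm takes it from 0.980 to 0.968. Section 3.2 states no allowance for losses, but the main issue here is bias.

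**The case against.** Ending participation is not the same as exclusion from analysis. Section 3.3 excludes nobody from any analysis, and section 3.2 says that all analyses follow intention to treat. A reader might infer that the two sections contradict each other outright. The text does not support that: the conflict is practical and arises because the outcome is not collected.

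A reader might also infer that non-adherent women are to be removed. The wording is permissive; only retrospective ineligibility is mandatory. Following the design is not defined either. Nothing equates it with attending sessions, and section 3.5 only encourages practice between them.

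It is tempting to say that both triggers act mainly on the training arm. That is inference. It is reasonable for non-adherence but weak for ineligibility, since both arms are screened before randomisation and both attend the TSST.

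Nor is it settled that the mandatory rule reaches events arising after allocation. Several exclusion criteria in section 3.4, such as analgesic use or current psychological treatment, could begin later, but the retrospective qualifier may govern both halves of the sentence. Leaving out women who were ineligible at entry can be defended if this is judged blind to arm and outcome. The rule also protects participants, and a statistical review should not replace it with continued exposure to the TSST.

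Finally, analysis sets and missing-data methods may be set out in a statistical analysis plan that is not at hand. That is fair for the analysis, but no such plan can recover saliva that was never collected. The collection rule belongs in section 3.3.

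These objections narrow the point. They leave standing that a woman stopped before the TSST has no primary outcome and that the stated carry-forward rule cannot provide one.

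**Conclusion.** The point holds in a limited form. Sections 3.2 and 3.3 can both be followed to the letter, yet the intention-to-treat promise then fails for the primary outcome of any woman stopped before the TSST. For the discretionary non-adherence trigger the loss plausibly falls mostly on the training arm; for retrospective ineligibility it could arise in either.

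The size cannot be derived from the protocol. Under the stated assumptions the shift is about 0.06 to 0.18 SD across both calculations, which is modest, and type I error stays below 0.09. A reader might infer that the bias favours the training. It does so only if the women removed are more stress-reactive than the rest, and no part of the protocol says so.

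The change is worth making because it is cheap and must be settled before data collection.

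**What to change.** In section 3.3, separate ending the training from ending outcome collection. State that:
- missed sessions or other deviations unrelated to safety do not by themselves end outcome collection;
- these women are still invited to the TSST and the questionnaires;
- every randomised woman is analysed in the arm to which she was assigned.

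Leave stopping for safety, for adverse events or at the woman's own wish as written.

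For retrospective ineligibility, sections 3.2 and 3.3 must be reconciled. Say whether the rule covers only facts present before randomisation. Have any exclusion from analysis judged blind to arm and outcome, and report such cases by arm.

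The cost is a few sentences. The reimbursement budget in section 6.1, CHF 2500 at CHF 50 each (section 5), covers 2500/50 = 50 women, so test visits for all 48 are already provided for. The statistical downside is a slight dilution of the effect by women who attended little of the training.

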***3.4 Inclusion and exclusion criteria***

Inclusion criteria are being between 18 and 60 years old, female gender and healthy by self-report statement, thus no known current or chronic somatic diseases or psychiatric disorders. Exclusion criteria are male gender, any acute or chronic disease (chronic pain, hypertension, heart disease, renal disease, liver disease, diabetes) as well as skin pathologies, neuropathies or nerve entrapment symptoms, sensory abnormalities affecting the tactile or thermal modality, current medications (psychoactive medication, narcotics, intake of analgesics) or being currently in psychological or psychiatric treatment, insufficient German language skills to understand the instructions, previous participation in studies using the TSST and daily consumption of more than three alcoholic standard beverages per day (a standard alcoholic beverage is defined as either 3dl beer or 1 dl wine or 2cl spirits).

***3.5 Explanations of the used variables***

***Independent Variable:*** *tend-and-befriend training (TBT)*

Participants will attend a group-based tend-and-befriend training (TBT). The intervention will be conducted in group format, led by two supervised master students. The intervention will first address the rational of the intervention, thus the psychobiological effects of stress, the importance of the social support and integration for health and well-being. The main stake of the intervention is devoted to small group-based exercises to promote social and emotional intelligence of the participants, improve interpersonal communication to improve the quality of their interpersonal interactions, and give room for personal and interpersonal exploration. During the intervention participants are encouraged to build new supportive relationships and to strengthen or revive existing interpersonal ties to both receive and give their support to others. Finally, scenarios of acute and chronic stress situations will be discussed, and the participants will train to adopt more social support based strategies in their coping repertoire. The participants will be encouraged to practice the skills with each other or other close relations between the sessions. For the intervention’s detailed description, please see Attachment 1. Since the intensity of endocrine response in females depends on the hormonal phase and the use of oral contraceptives (Kirschbaum et al., 1999), this information will be collected directly before the TSST and considered by the test evaluation.

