Attachment**: Manual for the tend-and-befriend training (TBT)**

**Session 1**

Duration: 4h

Goals: Interpersonal communication skills

Documents: Non-disclosure agreement

**Psychoeducation** (30min)

- Function of stress, effects of chronic stress, long-term effects on psychological and somatic health, stress as uncontrollable social evaluation
- Effects of social support on stress, health and wellbeing

**Group cohesion I** (30min)

- Discuss in small groups: What are my hopes and expectations from the course? Collect the inputs, whole group discussion
- Importance of safety in the training, signing of non-disclosure agreement

**Break** (15min)

**Group cohesion II** (60min)

The entire group together builds “Lauf der Dinge” domino like system out of different pieces and parts. The goal is to build a chain of objects that will put each other in movement to cross a few meters distance. The fun and non-competitive task is meant to promote group cohesion. Participants get to know each other in a relaxed way. We make photos that will be shown at the end of training.

**Break** (15min)

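### Training is given in groups in one arm only, and the named analyses and N = 48 make no allowance for it; if outcomes correlate within training groups, the standard errors are too small

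*Protocol*

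**What the plan says.** Section 3.1: "Subjects are randomized into the two conditions". Section 3.3 shows that this is done woman by woman, with individual codes in numbered envelopes. The control arm is a waitlist that receives the training only once the study is over.

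Section 3.5, on the training: "The intervention will be conducted in group format, led by two supervised master students". The same section encourages participants to practise with one another between sessions. The attached manual sets out six sessions totalling 16 hours (4 + 2 + 2 + 2 + 2 + 4). Of a whole-group task in Session 1 it says: "The fun and non-competitive task is meant to promote group cohesion". Later sessions use role-play by fellow participants, calls to a training partner and thanks to other members for their support.

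Section 3.2, on analysis: "Multivariate analyses of covariance and variance for repeated measures will be computed to analyse endocrine and psychophysiological stress responses". Regression is named for associations between psychological and cortisol measures. On size, it gives "the optimal total sample size of N = 48" for a large multivariate effect (f² = 0.35) with "power = 0.85 and α = 0.05 was calculated a priori with the statistical software G-Power". It mentions no training-group or trainer term, no ICC and no design effect. The number and size of training groups are not stated anywhere. The groups of three or four in Session 1 are exercise subgroups, not training groups.

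**The concern.** Women who train together share trainers, group climate and each other's support. Here mutual support is the hypothesised active ingredient, so groups that work well and groups that do not would deliver different amounts of treatment. That would make outcomes within a training group more alike than outcomes across groups. Waitlist women have no such grouping when they are measured.

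An analysis that counts the TBT women as independent then understates the variance of the TBT mean. Confidence intervals for the average effect come out too narrow and p-values too small. Part of what is reported as an effect of the training could belong to a particular group or trainer pair. The power calculation is optimistic for the same reason.

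**Working it through.** **Reproducing N = 48.** Using the noncentral F for an omnibus regression test with λ = f²·N, f² = 0.35, α = 0.05 and power 0.85, five predictors give N = 47, or 48 for equal arms (power 0.860 at 48). Five predictors is an assumption, because the protocol names neither the test nor the number of predictors. Four predictors give 44, six give 51, and a two-group comparison gives 28. None of these calculations contains a clustering allowance.

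**Inputs for the clustering check.**
- From the protocol: two arms, total 48, α = 0.05, groups in the TBT arm only.
- Assumed: 1:1 allocation (24 per arm); two-sided test; training groups of m = 6, 8, 12 or 24; ICC 0.02, 0.05 or 0.10.

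**Formulas.** The design effect in the TBT arm is DE = 1 + (m − 1)·ICC. In the waitlist arm it is 1. With equal arms and equal variances, true SE / reported SE = √((DE + 1)/2). The true level of a nominal 5% test of the average effect is 2·(1 − Φ(1.96 / SE ratio)).

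**Worked case.** For m = 8 and ICC 0.05, DE = 1 + 7 × 0.05 = 1.35. The SE ratio is √(2.35/2) = 1.084. The level is 2·(1 − Φ(1.96/1.084)) = 0.071.

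**All cases.** The last column simulates an ordinary t-test, 24 per arm, 100,000 trials per cell, with zero average effect and groups that differ.

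| Groups | ICC | DE | SE ratio | Level, formula | Level, simulated |
|---|---|---|---|---|---|
| 4 of 6 | 0.02 | 1.10 | 1.025 | 5.6% | 5.5% |
| 4 of 6 | 0.05 | 1.25 | 1.061 | 6.5% | 6.5% |
| 4 of 6 | 0.10 | 1.50 | 1.118 | 8.0% | 8.1% |
| 3 of 8 | 0.02 | 1.14 | 1.034 | 5.8% | 5.8% |
| 3 of 8 | 0.05 | 1.35 | 1.084 | 7.1% | 7.2% |
| 3 of 8 | 0.10 | 1.70 | 1.162 | 9.2% | 9.3% |
| 2 of 12 | 0.02 | 1.22 | 1.054 | 6.3% | 6.4% |
| 2 of 12 | 0.05 | 1.55 | 1.129 | 8.3% | 8.5% |
| 2 of 12 | 0.10 | 2.10 | 1.245 | 11.5% | 11.7% |
| 1 of 24 | 0.02 | 1.46 | 1.109 | 7.7% | 7.7% |
| 1 of 24 | 0.05 | 2.15 | 1.255 | 11.8% | 11.9% |
| 1 of 24 | 0.10 | 3.30 | 1.466 | 18.1% | 18.8% |

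At ICC 0 the simulated level is 5.0%.

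**What a correction does.** Take an assumed standardised difference d = 0.8 and ICC 0.05. A Welch-type test on TBT group means with Satterthwaite degrees of freedom stands in for the partially nested model. The uncorrected test has power of about 0.76.
- Group-means test: power about 0.64 with four groups, 0.57 with three and 0.49 to 0.50 with two. With two groups its level is still about 7.7%.
- Multiplying the SE by the ratio for a fixed ICC: power about 0.73 (m = 6), 0.71 (m = 8) and 0.68 (m = 12). The level stays at about 5.0 to 5.6% for groups of 6 to 12, provided the assumed ICC is right.

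**The case against.** A reader might infer that the standard errors are certainly too small and the 5% level is certainly lost. The protocol does not support that. It gives no ICC and no group size, so every figure above rests on assumed inputs, and at ICC 0.02 with groups of 6 the excess is close to trivial. Because women are randomised individually, if training affects nobody then sharing a group adds no correlation through training and the ordinary test is essentially valid. The inflation arises when the average effect is zero but groups or trainers differ. All of this stands, and it is why the point is conditional. It does not remove the problem of precision: whenever groups differ, the interval for the average effect is too narrow, whether or not that average is zero.

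The primary outcomes are cortisol and alpha-amylase in a stress test two weeks after training. The manual shows that cohesion is intended, but not that these responses cluster at 0.05 to 0.10. Clustering is more plausible for perceived social support. This also stands, and it is a reason to show a range that starts low.

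A reader might also infer that no planned analysis will account for training group. That goes too far, since a statistical analysis plan that is not shown could add a group term. But the protocol itself names the models and fixes N = 48 with no stated allowance, and a later model cannot separate group from training if only one group runs.

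**Conclusion.** The point holds in conditional form. The protocol combines individual randomisation, group delivery in one arm, and named analyses and a sample size that make no provision for training group. The reported precision of the arm difference is therefore overstated if outcomes correlate within groups. Under the assumptions listed, the overstatement ranges from slight (four groups of 6, ICC 0.02) to more than a doubling of the nominal level (two groups of 12, ICC 0.10). A single group of 24 is worse, because no analysis can then tell the training from the group that received it. The correction is worth making because it needs little work and the manual makes an ICC of exactly zero hard to defend. Enlarging the trial or changing how the training is delivered is not required to resolve the point.

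**What to change.** Record each TBT woman's training group and trainers, and state in section 3.2 how grouping will be handled for the cortisol, alpha-amylase and main questionnaire comparisons:

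- **At least four groups:** a partially nested mixed model, with a random group effect in the TBT arm only, waitlist women as singletons and small-sample degrees of freedom.
- **Two or three groups:** the group variance is too poorly estimated for that model to restore the 5% level reliably. Report the arm difference with SEs multiplied by √((DE + 1)/2) for assumed ICCs of 0.02, 0.05 and 0.10.
- **One group:** report the same sensitivity results and limit the conclusion to that group.

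Also state the number and size of training groups, and say that the 0.85 power assumes no clustering.

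The work amounts to recording group and trainers and a different model or SE multiplier. The statistical price is larger: wider intervals and the loss of power shown in the working. The fixed-ICC results are only as good as the assumed ICC, so all three values should be reported.
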